# Extended use of point-of-care technology versus usual care for in-home assessment by acute community nurses in older adults with signs of potential acute respiratory disease: an open-label randomised controlled trial protocol

**DOI:** 10.1186/s12877-024-04774-z

**Published:** 2024-02-16

**Keywords:** Point-of-care technology, Geriatric Assessment, Acute community nurse, Focused lung ultrasound

## Abstract

**Background:**

Due to ageing-related physiological changes, diagnosing older adults is challenging. Delayed disease recognition may lead to adverse health outcomes and increased hospitalisation, necessitating the development of new initiatives for timely diagnosis and treatment of older adults. Point-of-care technology, such as focused lung ultrasound scan and bedside analysis of blood samples (leucocytes with differential count, electrolytes, and creatinine) conducted in the patients’ home, may support clinical decision-making, and potentially reduce acute hospital admissions.

We present the protocol for a randomized controlled trial, which aims at assessing the effect of focused lung ultrasound scan and bedside blood analysis during in-home assessments among older adults with signs of potential acute respiratory disease on hospital admissions.

**Method:**

We will use a parallel open-label, individually randomised controlled trial design in an acute community healthcare setting. The trial will initiate on October 2022 and is expected to end one year later. The study population will include older adults (65 + year), with at least one of the following inclusion criteria: Cough, dyspnoea, fever, fall, or rapid functional decline. Expected study sample will comprise 632 participants. Participants in the control group will receive usual care, while the intervention group will undergo extended point-of-care technology (focused lung ultrasound scan and bedside venous blood analysis), in addition to usual care.

The primary outcome is acute hospital admission within 30 days follow-up. Secondary outcomes include readmissions, mortality, length of hospital stay, hospital-free days, complications during hospital admission, treatment initiations or changes, functional level, re-referrals to the acute community healthcare service, and contacts to the primary care physician. A tertiary outcome is the diagnostic accuracy of Acute Community Nurses for conducting focused lung ultrasound compared with a specialist. Outcomes will be analysed as intention-to-treat.

**Discussion:**

To our knowledge, this is the first randomised controlled trial examining the effect of extended use of point-of-care technology conducted in an in-home setting. We expect that the results may contribute to the development of new interventions aiming to improve timely diagnostics, treatment decisions, and reduce acute hospital admissions.

**Trial Registration:**

www.clinicaltrials.org NCT05546073 (Date of registration: September 19th, 2022).

**Supplementary Information:**

The online version contains supplementary material available at 10.1186/s12877-024-04774-z.

## Background

The population of adults aged 65 years and above is increasing, posing challenges to high-income countries’ primary and secondary healthcare systems [1, 2]. Of particular concern is the high rate of acute hospital admissions and in-hospital complications [3–9]. Recognising that timely treatment may prevent the progression to severe disease, it is imperative to identify and diagnose acute disease in older adults (65 + years of age) as soon as possible to avoid acute hospitalisation and functional decline [9–11]. Diagnosing older adults can be challenging due to ageing-related physiological changes [12, 13]. Moreover, many older adults do not present with typical symptoms; for example, coughing is a less prominent symptom of pneumonia [14]. Instead, older adults often exhibit atypical symptoms, such as delirium, falls, and rapid decline in physical functions, which are common proxy symptoms for infections [15].

Worldwide, lower respiratory tract infections rank among the most common reasons for hospitalization among older adults [16–18]. Given the challenges of diagnosing older adults and preventing acute hospital admission, a comprehensive approach is needed. This requires clinical examination, assessment of vital signs, and use of diagnostic tools, as well as biochemical results [12].

Point-of-care technology (POCT) allows tests or examinations to be carried out bedside, i.e., in the patient’s own dwelling, providing rapid answer in less than 20 min, depending on the instruments used [19, 20]. In primary care, commonly used POCT includes tests for glucose, International Normalized Ratio (INR), and C-reactive protein [21]. In recent years, new POCT for blood-analyses, such as leucocytes, creatinine, electrolytes, have been developed; however, they are not widely used in primary care [22]. As POCT may be used in a home-setting, it seems to be well-suited for older adults as diagnostics tools may support timely clinical decision making [21].

Point-of-care ultrasound (POCUS) has become a diagnostic tool for acute respiratory diseases over the last couple of decades. Studies have shown, that in the hands of a trained health-professional, focused lung ultrasound (FLUS), is an accurate tool for diagnosing pulmonary oedema, pneumothorax, pleural effusion, and pneumonia in emergency departments and intensive care units. [23–25]. However, there is no knowledge about its use and effects on the diagnostic process during in-home assessments. Only few studies have investigated FLUS as a diagnostic tool for pneumonia in primary care, but these studies were not representative for the geriatric population [26, 27].

The objective of this trial is to investigate whether extended POCT, including FLUS and bedside blood analysis, during in-home assessments among older adults with signs of potential acute respiratory disease, reduces hospital admission. Our primary hypothesis is that implementation of extended POCT in this context will result in a reduction in hospital admissions within 30 days compared to individuals receiving usual care, constituting our primary outcome. Additionally, we anticipate that the extended POCT will improve the accuracy and timeliness of bedside diagnostics, leading to enhanced clinical decision-making by primary care physician – reflecting our secondary outcomes and tertiary outcomes. Finally, we hypothesize that the intervention will lead to earlier identification of conditions and diseases, subsequently influencing factors such as hospital length of stay, amount of home care, and functional status during the 30 days follow up. This early diagnosis is expected to prevent functional decline, aligning with our secondary outcomes.

## Methods

This protocol paper is reported in line with SPIRIT statements [28], and the trial was registered at www.clinicaltrials.gov (Trial registration: NCT05546073, date of registration: September 19th, 2022). Any protocol amendments or modifications will be registered at www.clinicaltrial.gov.

### Study design

The trial is an open-label individually randomised controlled trial that investigates whether extended use of POCT for in-home assessment among older adults aged 65 and older reduces the rate of acute hospital admissions compared with usual care. The trial will use a parallel group design with a 1:1 allocation ratio, and a superiority design.

### Study setting

The trial is conducted in Kolding Municipality, Denmark, covering an area of 604.5 km^2^ with a population of 93,161 people, of whom 18,453 are aged 65 years or older [29].

In 2018, it was enforced to all Danish municipalities to establish an Acute Community-based Health Care Service (ACHCS) to enhance the timely recognition of acute disease [30]. While municipalities had the freedom to organise the ACHCS, most introduced an outgoing function from community healthcare centres, operated by Acute community nurses (ACNs).

The ACHCS in Kolding Municipality has a stationary function and an outgoing function, with ACNs dedicated to the outgoing function. The ACNs conduct in-home assessments primarily for older vulnerable citizens with acute signs of health deterioration. Approximately 5 – 8 patients are referred daily for in-home assessment due to suspected emerging acute disease. Referrals are mainly made by PCPs, but hospital physicians and home care personnel also have the capability to make referrals. If home care personnel refer patients, the PCP will be notified and responsible for diagnosis and treatment.

The assessment of acutely ill patients includes a clinical assessment, objective vital status parameters (oxygen level, respiration frequency, pulse, blood pressure, temperature), and, when appropriate, on-site POCT for biochemical analyses, e.g., CRP and haemoglobin. All results are communicated to the PCP or the hospital physician, providing them with clinical, objective information that qualifies diagnosis and medical decision-making.

### Study participants

Participants eligible for this study are people aged 65 years or older, referred to the ACHCS in Kolding Municipality for an in-home assessment.

The participants must have at least one of following symptoms of respiratory disease: cough, dyspnoea, fever, fall, or recent functional decline, defined as subjective (not able to perform normal daily activities as usual) or objective functional decline (increased need of home care). Falls and functional decline are not directly symptoms of respiratory disease, but are known as vague and atypical disease presentation; which is why we included them as signs of potential respiratory disease [31, 32].

Participants with known moderate to severe cognitive impairment are excluded from the study due to Danish legislation and the Regional Committees on Health Research Ethics for Southern Denmark.

### Recruitment and enrolment

Patients referred to the ACHCS are visited by an ACN in their own dwelling, which may include a private house, care-home, or rehabilitation centre. If the patient fulfils the inclusion criteria, the ACN provides comprehensive information about the study both orally and in writing. Subsequently, the patient is given the opportunity to sign the informed consent document. Additional files 1 and 2 contain details pertaining to the informed consent process and written participant information. These documents have received approval from the Regional Committees on Health Research Ethics for Southern Denmark.

### Randomization, allocation, and implementation

The allocation sequence of randomisation numbers is generated using an online random number service, carried out by a data manager from Open Patient Data Exploratory Network (OPEN) [33] and the primary investigator, [name]. Randomisation numbers are paired with the REDCap® database (version: REDCap 9.1.15—© 2020 Vanderbilt University) developed for this trial by the primary investigator [34, 35]. Upon obtaining the participant’s signed informed consent, the ACN will register the participant in the trials database. The database employs a random allocation system, assigning a unique computerized randomization number to each participant. All parties involved, including participants, ACNs, and PCPs are aware of group assignment. Figure 1 shows the study flow.

**Fig. 1 Fig1:**
[figure not shown]
Study Flow Chart. ACHCS, Acute Community Health Care Service; POCT, Point-of Care Technology; CRP, C-reactive Protein; Hb, Hemoglobin; PCP, Primary Health Care Physician

### Intervention and control

In the control group, the ACN will carry out usual care, which involves a clinical inspection, measurements of vital signs (respiratory rate(breaths/min), saturation (%), blood pressure (mmHg), heart rate (beats/min), body temperature (C^0^), and Glasgow Coma Scale [36]), and POCT for CRP and haemoglobin.

The intervention group will receive extended POCT in addition to usual care. Extended POCT includes a FLUS and biochemical blood analyses. Biochemical blood analyses include sodium, potassium, creatinine, urea, and leucocytes with differential count.

In both control and intervention groups, the ACN communicates the examination results to the participants’ PCP through telephone communication and electronic message (EdiFact) for written documentation. The communication to the PCP is part of usual care and is carried out in both groups.

Preceding to commencement of the study, all ACNs undergo comprehensive training in FLUS, technical procedure of POCT biochemical blood-analysis, as well as training in research methods with a specific emphasis on study procedures. This training is designed to enhance their adherence to and compliance with the randomization procedure and protocol.

### FLUS

The training program for ACNs in FLUS encompasses four integral modules: The initial module involves online training (Module 1). This entails theoretical instruction in sonographic physics, knobology, and sonographic findings related to FLUS. Module 1 is delivered through an e-learn platform (Plan2Learn ApD, Viby, Denmark) with a validated theoretical test in FLUS [37]. Successful completion is a prerequisite for advancing to Module 2—Immersive Virtual Reality-FLUS training. Module 2 is developed by Vita-Sim (VitaSim ApS, Odense, Denmark) and [name] ([name]) (Department of Radiology, Odense University Hospital) [38]. Following Module 2, ACNs proceed to Module 3 hands-on FLUS-training, provided by the primary investigator. Subsequent to this, ACNs engage in supervised daily FLUS-training for approximately two months (Module 4).

Certification of ACNs in FLUS is required upon their evaluation through the validated objective structured assessment of technical skills tool for point-of-care lung ultrasound imaging (LUS-OSAUS), conducted at intermediate level [39].

FLUS is performed using Lumify® C5-2 Curved Array Transducer (Philips Medical Systems, Bothell, WA), lung preset, with a bandwidth of 5–2 MHz and scan depth up to 30 cm.

A standardized protocol, previously validated in patients with acute respiratory symptoms, guide FLUS diagnostic criteria during the trial [24, 40]. These criteria align with international recommendations [41–43]. ACNs document conclusive findings (See Additional file 3). All FLUS examinations will be stored digitally, and undergo blinded assessment by a specialist throughout the RCT. The ACNs will receive feedback on their FLUS during the RCT once a week by primary investigator.

In instances where ACNs encounter challenges in interpreting FLUS findings during in-home assessments, the option of tele-ultrasound through Cisco Webex® (Cisco system, Inc., San Jose, U.S.A) is available. This functionality facilitates online video calls, enabling ACNs to seek guidance from the primary investigator. Utilization of Webex® is recorded, along with reasons for its application during the study period.

### Venous blood samples

Medical laboratory technologists from Hospital Lillebaelt, Kolding Hospital, will train ACNs in correct venous blood sample techniques.

POCT on blood samples for creatinine and electrolytes involves venous blood samples collected in lithium/heparin vacutainers. The samples are immediately analysed using the i-STAT® (Abbott, Inc., NJ, U.S.A.) with the CHEM8 cassette.

For POCT blood analysis of leucocyte differential count, venous blood samples are collected in EDTA-vacutainers and analysed immediately on the HemoCue® WBF DIFF System (HemoCue AB, Ängelholm, Sweden) with dedicated micro-cuvettes.

Additionally, POCT blood-analysis for CRP is conducted using blood samples obtained by finger-prick and analysed on the QuickRead go® instrument (Orion Diagnostica, Oy).

Technical handling of all POCT instruments will be demonstrated by the POCT-companies.

Routine venous blood samples will be collected monthly to validate the POCT equipment. The samples will be analysed at the Department of Biochemistry and Immunology, Hospital Lillebaelt, Kolding Hospital, within 6 h. To maintain sample integrity during transport, the samples will stored in a controlled cabinet, maintaining a stable temperature of 20 °C.

### Research training session

All ACNs will receive a research training session on “How to conduct research”, with specific focus on informing eligible participants about the trial, and the importance of adherence to protocol. The primary investigator is responsible for conducting the research training session.

### Outcomes

The primary outcome of this trial is the rate of hospital admission within 30-days follow-up. Secondary outcomes, along with their definitions, are listed in Table 1. The tertiary outcome involves evaluating ACNs diagnostic accuracy in conducting FLUS compared with a FLUS-specialist. A FLUS specialist will perform blinded assessment of all FLUS video clips. Outcome measures will include sensitivity and specificity, PPV and NPV, with a Bland-Altmann analysis. The results of the tertiary outcome will be reported in a separate paper.

**Table 1 Tab1:** Primary, secondary, and tertiary outcomes

	**Outcome**	**Outcome measure**

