***Tertiary outcomes***		
Outcome 14	ACNs diagnostic accuracy for conducting FLUS compared with a FLUS-specialist	ACNs conclusions are index test and FLUS-specialist conclusions used as reference test

*ACNs* Acute community Nurses, *ACHCS* Acute Community Health Care Service, *FLUS* Focused Lung Ultrasound, *PCP* Primary Care Physician

^a^Day 0: Defined by Day of inclusion

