### Supervision and access to a physician

This trial is the first to investigate whether ACNs can conduct FLUS and extended POCT on blood biochemistry during in-home assessment of older adults. While ACNs have substantial clinical experiences and conduct delegated examinations for PCPs, as FLUS is not widely used in primary care, they will be dependent on supervision for the interpretation of scans by the primary investigator. All contacts with the research team will be registered in the database.

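### The tertiary outcome is named as nurses' accuracy in conducting lung ultrasound, but the comparison can only measure how they interpret their own clips

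*Protocol article*

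**What the plan says.** The Outcomes section of the protocol article defines the aim: "The tertiary outcome involves evaluating ACNs diagnostic accuracy in conducting FLUS compared with a FLUS-specialist". Table 1 repeats it for Outcome 14 ("ACNs diagnostic accuracy for conducting FLUS compared with a FLUS-specialist") and fixes the two tests: "ACNs conclusions are index test and FLUS-specialist conclusions used as reference test". The Abstract uses the same idea of conducting the scan.

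The specialist's conclusion comes from recorded material. The Outcomes section says "A FLUS specialist will perform blinded assessment of all FLUS video clips", and the FLUS section says "All FLUS examinations will be stored digitally, and undergo blinded assessment by a specialist throughout the RCT". The stored examinations are those made by the nurses during home visits. The article names no repeat scan by the specialist, no chest imaging and no final diagnosis as a reference.

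Results are to be expressed as accuracy measures: "Outcome measures will include sensitivity and specificity, PPV and NPV, with a Bland-Altmann analysis". They will appear in a separate paper.

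**The concern.** Conducting a scan has two parts: obtaining views that show the pathology, and reading them correctly. Here the index and the reference share the first part. If a lesion was never recorded, the specialist has nothing to find, so the patient is reference-negative whatever the truth. Such a patient leaves the denominator of sensitivity and, if the nurse also concludes negative, counts as a true negative.

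What is at stake is the conclusion drawn from the tertiary paper. Sensitivity and NPV published under this label would be taken to show how well a nurse-performed home scan detects disease. The comparison can support a narrower statement: how well nurses read the clips they obtained.

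**Working it through.** **Plan's own figure.** None exists for this outcome. The sample size in the article (602, or 632 with dropout) concerns the primary outcome and does not bear on the point.

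**Step 1: stated items side by side.**
- Property named: accuracy in conducting FLUS (Abstract; Outcomes; Table 1).
- Index test: the nurse's conclusion (Table 1).
- Reference test: the specialist's conclusion (Table 1), reached from stored clips (Outcomes; FLUS).
- Independent acquisition: none described.

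The mismatch is between items that the article itself states, so it does not depend on anything left to a fuller document.

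**Step 2: what the reported sensitivity estimates.** Let *a* be the share of diseased patients whose pathology is on the clips, and Se and Sp the nurse's reading sensitivity and specificity. With an accurate specialist:
- reported sensitivity = Se, for every value of *a*;
- whole-scan sensitivity = *a* × Se + (1 − *a*) × (1 − Sp).

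The second term is the chance that a nurse calls a patient positive although the pathology was not captured. The documents give none of these quantities. Assuming Se = 0.90 and Sp = 0.95 for illustration:

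| *a* | Reported | Whole scan | Gap (points) |
|---|---|---|---|
| 1.00 | 0.90 | 0.90 | 0 |
| 0.95 | 0.90 | 0.95×0.90 + 0.05×0.05 = 0.8575 | 4.25 |
| 0.90 | 0.90 | 0.90×0.90 + 0.10×0.05 = 0.815 | 8.5 |
| 0.80 | 0.90 | 0.80×0.90 + 0.20×0.05 = 0.73 | 17 |
| 0.70 | 0.90 | 0.70×0.90 + 0.30×0.05 = 0.645 | 25.5 |

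The gap is (1 − *a*) × (Se + Sp − 1). It is positive whenever *a* < 1 and reading is better than chance.

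**Step 3: NPV, same assumptions, with prevalence 0.30 (also assumed) and *a* = 0.90.** Captured pathology is 0.30 × 0.90 = 0.27 of patients, and uncaptured pathology 0.03.
- Nurse-negative: 0.27×0.10 + 0.73×0.95 = 0.027 + 0.6935 = 0.7205.
- Reported NPV: 0.6935 / 0.7205 = 0.963.
- Whole-scan NPV: (0.70×0.95) / 0.7205 = 0.665 / 0.7205 = 0.923.

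**Step 4: let the specialist err too.** Take prevalence 0.30, *a* = 0.90, specialist sensitivity and specificity both 0.95, and independent errors.
- Specialist-positive: 0.27×0.95 + 0.73×0.05 = 0.293.
- Both positive: 0.27×0.95×0.90 + 0.73×0.05×0.05 = 0.2327.
- Reported sensitivity: 0.2327 / 0.293 = 0.794, which is below the whole-scan 0.815.

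With specialist specificity 0.98 instead, reported sensitivity is (0.27×0.95×0.90 + 0.73×0.02×0.05) / (0.27×0.95 + 0.73×0.02) = 0.2316 / 0.2711 = 0.854, which is above 0.815. The net direction therefore depends on how well the specialist reads. In neither case does the comparison reveal what was not captured.

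**The case against.** The strongest reply is that the comparison is disclosed. Table 1 sets conclusion against conclusion, and the text says that the specialist sees clips, so only the word for conducting is at fault. That is largely right, and it is why the essential remedy is a change of wording. The wording still matters, because it determines what the accuracy figures will be taken to show.

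A second reply is that acquisition skill is handled elsewhere: "Certification of ACNs in FLUS is required upon their evaluation through the validated objective structured assessment of technical skills tool". The FLUS section also describes about two months of supervised daily scanning, a standardised scanning protocol and weekly feedback. These make poor acquisition less likely. They lie outside Outcome 14 and do not bring acquisition in the trial's home scans into its sensitivity or NPV.

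Three stronger readings are tempting but not supported:
- A reader might infer that reported sensitivity will be too high by a known amount. Every input to such a figure is assumed, and specialist error can reverse the net bias.
- A reader might infer that poor or incomplete clips are scored as agreement. The article does not say how they are scored, and that detail may properly sit in a fuller document. A specialist may well notice a missing zone or a poor image. What stays hidden is a lesion outside adequately recorded views.
- A reader might take the Discussion, under Supervision and access to a physician, as a statement about Outcome 14: "This trial is the first to investigate whether ACNs can conduct FLUS and extended POCT". That sentence describes the trial as a whole and mentions neither Outcome 14 nor the clip reading.

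**Conclusion.** The point holds as a mismatch between the outcome's name and what the design can measure. Outcome 14 yields accuracy of, or agreement in, interpretation of nurse-acquired clips. Read as performance of the whole scan, sensitivity and NPV carry an upward bias from uncaptured pathology. That bias is nil if capture is complete and grows as capture falls; specialist reading error can offset or outweigh it. On the assumed values the sensitivity gap runs from 0 to about 25 points as capture falls from 100% to 70%. That range shows how the mechanism works and is not an estimate for this trial.

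The matter is minor. The outcome is tertiary and reported separately, and the primary conclusion and the sample size do not depend on it.

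**What to change.** Restate the tertiary outcome, in Table 1 and in the separate paper, as accuracy or agreement of nurses' interpretation of nurse-acquired clips against the specialist's reading, and limit the conclusions to that.

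In the specialist's reading of the stored clips, also record whether each scan is complete and of diagnostic quality. Report that proportion, and add a sensitivity analysis in which inadequate scans count as index-test failures.

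The rewording costs almost nothing. The adequacy rating is one extra field. However, inclusion was expected to end on 31 August 2023 and clips were to be assessed during the trial, so some may need re-reading; their digital storage makes that possible. The figures may become less favourable. Even with the rating, a lesion outside adequately recorded views goes undetected, so the rating does not replace the restatement.

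### The Bland-Altman analysis planned for the tertiary outcome does not fit readings defined as diagnostic conclusions; use a categorical agreement statistic or name the continuous quantity

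*Protocol article*

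**What the plan says.** The Outcomes section of the protocol article makes the nurses' diagnostic accuracy with focused lung ultrasound (FLUS) the tertiary outcome, to be reported in a separate paper. On the measures it says: "Outcome measures will include sensitivity and specificity, PPV and NPV, with a Bland-Altmann analysis". On the reference reading it says: "A FLUS specialist will perform blinded assessment of all FLUS video clips".

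The tertiary row of Table 1 defines the two readings: "ACNs conclusions are index test and FLUS-specialist conclusions used as reference test". The FLUS section likewise has the nurses record conclusive findings and points to Additional file 3, which is not among the documents.

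The FLUS section also provides live help: "In instances where ACNs encounter challenges in interpreting FLUS findings during in-home assessments, the option of tele-ultrasound" by video call is available, "enabling ACNs to seek guidance from the primary investigator". The use of this help is logged: "Utilization of Webex® is recorded, along with reasons for its application during the study period". The section on supervision and access to a physician says of the nurses that "they will be dependent on supervision for the interpretation of scans by the primary investigator", and that contacts with the research team are registered in the database. The article does not say whether guided scans are pooled, excluded or shown separately in the accuracy analysis.

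**The concern.** Sensitivity, specificity and the predictive values classify each scan as positive or negative for a finding. A Bland-Altman analysis does something else: it takes two measurements on one numerical scale and describes the mean and spread of their differences. The article attaches both to the same comparison but describes only conclusions.

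If the analysis is run as written on coded conclusions, the separate paper would carry a bias estimate that can look reassuring whatever the quality of the reading, because missed and over-called findings cancel. The limits would be values that no single pair of readings can take.

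A smaller question is what the accuracy figures describe. Some conclusions may be reached with the primary investigator's help, and the reference reader assesses stored clips that the nurse acquired. Both affect how the result should be labelled.

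**Working it through.** **Inputs.** From the article: both readings are conclusions (Table 1), the five measures listed in Outcomes, and the availability and logging of tele-ultrasound (FLUS section). The article gives no accuracy target, expected prevalence, share of guided scans, or accuracy with and without guidance, so there is no stated figure to reproduce. Every prevalence and accuracy value below is an assumption for illustration.

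**1. Bland-Altman on present/absent readings.** Code each reading 1 or 0 and take nurse minus specialist. The difference can only be -1, 0 or 1. Write p for prevalence by the specialist's reading.

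- Missed: b = p × (1 - sensitivity)
- Over-called: c = (1 - p) × (1 - specificity)
- Bias = c - b, which is the nurse's positive rate minus the specialist's
- SD = √(b + c - bias²); limits = bias ± 1.96 × SD

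With p = 0.20:

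| Reader | b | c | Bias | SD | Limits |
|---|---|---|---|---|---|
| Sensitivity 0.60, specificity 0.90 | 0.20 × 0.40 = 0.08 | 0.80 × 0.10 = 0.08 | 0.00 | √0.16 = 0.40 | ±0.78 |
| Sensitivity 0.80, specificity 0.95 | 0.20 × 0.20 = 0.04 | 0.80 × 0.05 = 0.04 | 0.00 | √0.08 = 0.283 | ±0.55 |

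The first reader misses 40% of positive scans and still shows no bias. The limits do differ, but only because, when the bias is zero, they are 1.96 times the square root of the proportion of discordant pairs. That proportion is easier to read directly.

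**2. The same two readers with a categorical statistic.** Both readers have a positive rate of 0.20, equal to the specialist's, so chance agreement is 0.20 × 0.20 + 0.80 × 0.80 = 0.68.

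- First reader: observed agreement 1 - 0.16 = 0.84; kappa = (0.84 - 0.68) / (1 - 0.68) = 0.50. Positive agreement = 2 × 0.12 / (0.20 + 0.20) = 0.60; negative agreement = 2 × 0.72 / (0.80 + 0.80) = 0.90.
- Second reader: observed agreement 1 - 0.08 = 0.92; kappa = (0.92 - 0.68) / 0.32 = 0.75. Positive agreement = 2 × 0.16 / 0.40 = 0.80; negative agreement = 2 × 0.76 / 1.60 = 0.95.

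These figures separate the two readers and show where the disagreement lies. The Bland-Altman bias does not.

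**3. Guided scans.** If a share f of scans is guided, pooled sensitivity = (1 - f) × unaided + f × assisted, so pooling shifts it by f × (assisted - unaided). Assume f from 5% to 30%, unaided sensitivity 0.70 to 0.90 and assisted sensitivity 0.90 to 1.00. The shift then runs from 0 (assisted and unaided both 0.90) to 0.30 × (1.00 - 0.70) = 9 percentage points. A middle case is 0.10 × (0.95 - 0.80) = 1.5 points. The upward direction is built into this range, because assisted sensitivity was never set below unaided. It is not a result from the document.

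**The case against.** The best defence of the Bland-Altman analysis is that Additional file 3 is not shown and might contain a numerical item. That cannot be excluded. It does not rescue the text as it stands: the article names no such item, and Table 1 specifies conclusions. Nor is the mean difference on 0/1 readings strictly meaningless, since it is the difference in positive rates; it simply does not measure accuracy or agreement. The monthly laboratory validation of the blood analysers does involve continuous readings, but it is a separate activity, and the Outcomes section ties Bland-Altman to the nurse-specialist comparison.

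A reader might go further and infer that the plan counts guided scans as the nurses' own work and that the accuracy figures are therefore inflated. The wording of Table 1, which makes no exception for guided scans, invites this, but the document does not support it:

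- The article is silent on how guided scans are handled. It logs them, so they can be separated, and such detail is commonly left to an analysis plan.
- It does not say that the primary investigator who gives guidance is the blinded specialist, so help need not move readings towards the reference.
- It makes no claim for unsupervised use; it says openly that the nurses will depend on supervision. Accuracy with support available is a legitimate target.

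Restricting the main analysis to unguided scans would also be a poor remedy. Suppose 20% of scans are guided, unguided scans reach 80% sensitivity, and guided scans reach 95% but would have reached 60% unaided. Pooling gives 0.8 × 0.80 + 0.2 × 0.95 = 83%, wholly unaided reading would give 0.8 × 0.80 + 0.2 × 0.60 = 76%, and restriction gives 80%. The restricted figure is still 4 points too high in this example, because the hardest scans have been dropped.

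Finally, the clip-based reference is openly described, and acquisition skill is addressed through certification and a standardised scanning protocol. What remains is a wording point: the outcome is labelled as accuracy in conducting FLUS, while a reference reader of stored clips cannot see what was not recorded.

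**Conclusion.** The point holds for the Bland-Altman analysis: as described, it does not fit the data. Its bias can be zero for a reader who misses 40% of positive scans (assumed prevalence 20%, specificity 0.90). This conclusion rests on both readings being categorical, as Table 1 states, and would change only if an unnamed numerical score exists.

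Sensitivity, specificity, PPV and NPV against a blinded reading suit the question and are not in doubt. On guided scans, the only supportable point is that results should be shown by guidance status and labelled accordingly; neither the size nor the direction of any bias can be established from the document.

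Severity is low. This is an added statistic for a tertiary outcome, and the primary analysis is unaffected.

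**What to change.** 1. In the Outcomes section, replace the Bland-Altman analysis with a categorical agreement statistic for each FLUS finding, for example Cohen's kappa with positive and negative agreement, beside sensitivity, specificity, PPV and NPV. Alternatively, name the continuous quantity for which Bland-Altman is intended and keep it for that quantity only.
2. State that accuracy will be reported for all scans, and separately for scans with and without tele-ultrasound guidance, using the log already kept. Do not make the unguided subset the main result. An analysis of the nurse's conclusion before a call should be offered only if that conclusion was recorded, which the article does not say.
3. Describe the result as agreement on the interpretation of nurse-acquired clips.

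The cost is a change of analysis and reporting wording, with no new data and no effect on sample size. The guided group may be small, so its estimates may be imprecise.
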